## 2 Rationale / Background

### Background summary

Breast cancer is a common disease, affecting 1 in 8 women over the course of their life (Cancer Australia 2023). In 2020, the worldwide incidence of BC was 2.26 million (Ferlay et al., 2020). Fortunately, survival rates from BC have improved dramatically such that currently, 9 out of 10 women remain in remission at 5 years following initial diagnosis (Giaquinto et al., 2022). Treatment for BC often includes surgical excision of the tumour and affected lymph nodes, chemotherapy, endocrine therapy and/or radiotherapy. Side effects of BC treatments include but are not limited to loss of skeletal muscle mass, reduced cardiovascular fitness, fatigue, pain, depressive symptoms and gastrointestinal symptoms (Bland 2019, Collins 2018, Feliciano 2017, Mijwel 2018). These side effects can persist for many years and serve to reduce health-related quality of life and physical function (Brown 2012). Addressing quality of life following treatment is of paramount importance, particularly with reports of

worsening quality of life 2-years after diagnosis (Ferreira 2019). Implementation of therapies and/or strategies to address these sequelae is urgently needed.

Encouragement to exercise has become part of usual care during and following completion of BC treatment. Data from several systematic reviews investigating the effects of exercise demonstrate positive effects on overall health-related quality of life (Mishra 2012; Zhang 2019), pain (Plinsinga 2022), fatigue (Meneses- Echavez 2015), physical function (Ficarra 2021) and mood (Salam 2022). Further, exercise interventions have been shown to reduce declines in physical fitness (Ficarra 2021) and improve chemotherapy completion rates (van Waart 2015). Importantly, exercise post-diagnosis significantly reduces BC-related mortality (Salam 2022). Despite this growing body of literature, effect sizes are modest and wide confidence intervals published across systematic reviews challenge our confidence in that effects will be clinically meaningful. This highlights the need for ongoing research to optimize outcomes from exercise interventions.

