Engaging in regular exercise during chemotherapy is arguably more challenging relative to other phases of the treatment trajectory due to common and debilitating physical side effects, such as fatigue, nausea and cancer related pain (Kirkham 2014). Such side effects from chemotherapy are the most commonly reported barrier to adherence to exercise during chemotherapy treatment for women with breast cancer (Kirkham 2014). Other cited barriers include inconvenient exercise locations, disease stage and poor baseline strength or fitness (Courneya 2008, Gildea 2023). Currently, as part of usual care, people known to the Breast Clinic at RPH are seen by a physiotherapist who provides education regarding the importance of exercise during their cancer treatment. Patients are provided with a pamphlet and encouraged to engage in appropriate off-site exercise groups. It is understood that uptake of exercise is suboptimal. This study will explore the effect of an experimental exercise program, known as the *SMART* program. This intervention has been co-designed, along with people who have BC, to overcome many of the known barriers to exercising during their cancer treatment. The *SMART* program will include individualised exercise prescription, monitoring of adherence, goal setting, strategies to optimise social support, action and coping planning and regular 'coaching' support to guide individuals through their exercise intervention. Importantly, this intervention will be available to people known to RPH, but who cannot access RPH due to transport problems and because they live outside Perth (i.e. rural and remote regions).

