## **Intervention**

A randomised controlled trial will be conducted. The experimental group will receive the *SMART* exercise program. To optimise adherence, participants in the *SMART* exercise program will be offered weekly one-on-one sessions with a senior physiotherapist for exercise prescription, monitoring or exercise uptake and potential treatment side effects, and to facilitate behaviour change. The target behaviour of the *SMART* program is to assist participants to build up to or maintain 150 minutes per week of moderate intensity aerobic exercise (or 75 minutes per week of vigorous intensity exercise) as well as two resistance training sessions per week. This target has been informed by the 2019 American College of Sports Medicine (ACSM) guidelines for exercise and cancer. Specific details of the *SMART* program have been described in Section 4 (under Intervention / Product Description).

The principles underpinning the *SMART* exercise program are that it will be:

**Self-determined:** Participants will be in the driver's seat regarding the establishment of weekly goals. They can choose to engage in exercises they enjoy (walking, swimming, cycling, dance etc) at the time of day that suits them best. Due to expected variation in baseline fitness levels and exercise preferences, the program will be individualised to each participant.

**Monitored:** The monitoring of adherence and treatment fidelity will occur through exercise diaries, monitoring of heart rate during the supervised and unsupervised exercise sessions and regular questionnaire data to monitor potential side effects relating to BC treatment and exercise.

**Adaptable:** The participant can choose the days/times they want to exercise and whether the weekly (supervised) session is completed at RPH, or via telehealth. In addition, participants will be briefed to periodise exercise routines according to potential BC treatment side effects (e.g. fatigue, pain, nausea) reported used the above monitoring strategies. Specifically, exercise programs will be adapted if the participant reports any symptoms (e.g. if an individual reports post-exertional malaise for 24 hours following an exercise program and their heart rate reached 140bpm/80% of their predicted HR max, they will be instructed to reduce their heart rate intensity to 110bpm/60% of their predicted HR max for their next exercise session).

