### 3 Trial Aims / Objectives / Hypotheses

For all research questions, the study population refers to adults with newly diagnosed with breast cancer who are undergoing treatment through the Breast Clinic at RPH.

Primary research questions:

- 1) Does the SMART program, compared with usual care, change health-related quality of life (primary outcome) measured 16-weeks and 12-months following randomisation?
- 2) Does the SMART program, compared with usual care, change peripheral muscle strength, muscle mass, exercise tolerance, exercise adherence and chemotherapy completion rates (secondary outcomes) measured 16 weeks following randomisation?

Secondary research questions:

- 1) Do factors such as adherence, treatment pathway and cancer stage moderate the magnitude of any change in primary or secondary outcomes? (i.e. moderator analysis)
- 2) What is the health care utilisation, absenteeism and presenteeism over the 12 months following randomisation? (descriptive analyses only, to guide patient expectations in regarding these outcomes)

- 3) Does performance on tests of peripheral muscle force-generating capacity and exercise tolerance, change with test repetition (i.e. is there a learning effect)? (can be answered by Honours students enrolled in the BSc physiotherapy at Curtin University)
- 4) What is the minimal detectable difference in health-related quality of life and exercise tolerance? (can be answered by Honours students enrolled in the BSc physiotherapy at Curtin University)
- 5) Do psychological determinants of behavioural change, such as capability, opportunity, and motivation affect adherence to the SMART program and physical activity maintenance?
- 6) Does the SMART program improve mood, and does mood influence adherence to the program and physical activity maintenance?

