## OTHER VARIABLES

**Descriptive variables** will be recorded such as age, sex, body mass index, employment status, co-morbid conditions, stage of cancer and details of cancer treatment.

**Healthcare utilisation and adherence with exercise** will be assessed in both groups. In the control group, this will be documented during the monthly phone calls and exercise diaries. In the experimental group, this will be monitored by asking each participant during the weekly supervised sessions and also using exercise diaries (see Section 4, Monitoring). Regarding healthcare utilisation, we will ask each participant to recall the number of; (i) visits to the Emergency Department, (ii) inpatient admission days, (ii) outpatient appointments and, (iii) visits to any other healthcare provider (Y/N, who, number of visits). Regarding adherence with exercise, we will ask each participant to recall the number of minutes spent engaging in moderate or vigorous intensity exercise and details regarding any resistance exercise.

**Absenteeism and presenteeism** will be assessed using the iMTA productivity cost questionnaire (Bouwman 2015).

**Global rating of change** will be assessed by asking participants, on completion of the SMART exercise program, to indicate if their health-related quality of life or exercise tolerance had 'improved', 'worsened' or 'stayed the same'. Those participants who rated their walking ability as 'improved' or 'worsened' will then be asked to rate the degree of change on a seven-point scale (1 a little better to 7 a great deal better).

**Feasibility and acceptability** will be measured using; (i) Quantitative data from an acceptability and feasibility questionnaire, and (ii) qualitative data from exit interviews. These are described below:

*Quantitative data* will be collected using a questionnaire asking participants to rate their perceptions of the SMART exercise program (e.g., "*I thought the SMART exercise program was easy to understand*"). Participants can rate each item on a five-point scale (1 "*I don't agree at all*" to 5 "*I totally agree*"). Four open-ended items at the end of this questionnaire allow participants to include additional feedback (e.g., "*What did you like about the SMART exercise program?*").

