## 9 Data Management, Statistical Analysis and Record Keeping

## Statistics and Interim Analysis

*The primary research questions for this study are:*

- Does the SMART program, compared with usual care, change health-related quality of life (primary outcome) measured 16-weeks and 12-months following randomisation?

AND

- Does the SMART program, compared with usual care, change peripheral muscle strength, muscle mass, exercise tolerance, exercise adherence and chemotherapy completion rates (secondary outcomes) measured 16 weeks following randomisation?

The analyses for this research question will be performed according to the intention to treat principle. For the primary outcome, health-related quality of life, with 4 assessment points, linear models will be used to account for repeated measures with participant ID entered as a random effect. The primary time point of interest will be the end of the intervention phase. Group, time and group by time will be analysed as fixed effects and the baseline measure will be entered as a covariate to adjust for random baseline differences. Between group difference for the dependent outcome of chemotherapy completion (yes/no) will be analysed using logistic regression. Between group differences for the remaining secondary measures (peripheral muscle force-generating capacity, muscle mass, exercise tolerance) will be examined using linear regression with the corresponding baseline measure used as a covariate. Data transformations or alternative models (such as gamma distribution) will be considered if there is poor model fit.

Missing data will be examined and multiple imputations investigated (assuming they are missing at random). Models will be adjusted for covariates, randomisation variables and confounders such as age. Estimates of the effects will be reported with their corresponding 95% confidence intervals.

*The first secondary research question is:*

- Do factors such as adherence, treatment pathway and cancer stage moderate the magnitude of any change in primary or secondary outcomes? (i.e. moderator analysis)

To understand any moderator effects, the listed covariates will be entered into a multivariable model using the outcomes listed above. In addition, adherence will be examined to see if it mediates the relationship with the outcomes, by calculating the indirect through the use of partial coefficients.

*The second secondary research question is:*

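### The indirect effect of SMART through adherence can be confounded by treatment side effects, and adherence, which SMART is built to change, should not be listed as a moderator

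*Protocol*

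**What the plan says.** Section 3 asks, as the first secondary question: "Do factors such as adherence, treatment pathway and cancer stage moderate the magnitude of any change in primary or secondary outcomes". Section 9 (Statistics and Interim Analysis) repeats the question, enters the listed factors in a multivariable model, and adds that "adherence will be examined to see if it mediates the relationship with the outcomes, by calculating the indirect through the use of partial coefficients".

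The stated adjustment is general: "Models will be adjusted for covariates, randomisation variables and confounders such as age". The randomisation variables are treatment pathway, living in or outside Perth, and regular exercise before diagnosis (section 4, Blinding and Randomisation).

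On adherence, section 7 (Other variables) says: "Healthcare utilisation and adherence with exercise will be assessed in both groups". It comes from recall and diaries during the intervention.

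On side effects, the background says: "Such side effects from chemotherapy are the most commonly reported barrier to adherence to exercise during chemotherapy treatment for women with breast cancer". It also says: "These side effects can persist for many years and serve to reduce health-related quality of life and physical function". Under Intervention in section 2, "exercise programs will be adapted if the participant reports any symptoms".

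**The concern.** An indirect effect from partial coefficients is the product of two paths. The path from group to adherence is protected by randomisation. The path from adherence to outcome, given group, is not: its coefficient is causal only if nothing unadjusted drives both adherence and outcome. The protocol names something that does. Side effects lower exercise and lower quality of life, and SMART itself modifies the exercise when symptoms appear. Participants with more side effects would then exercise less and score worse, even if exercise had no effect on the score. Because SMART is meant to raise adherence, the first path is probably non-zero, and the product inherits the confounding of the second.

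Listing adherence as a moderator is a separate weakness. Treatment pathway and cancer stage describe the participant and are not consequences of allocation. Adherence is partly a result of allocation, so a given level of it identifies differently selected people in the two arms.

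At stake is the explanatory claim. The trial could report that adherence accounts for part of the SMART benefit when it does not.

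**Working it through.** **The plan's own figure.** The protocol gives no figure for the mediation analysis. Its sample size gives the scale: n per group = 2 × (1.96 + 0.842)² × 20.52² / 8² = 103.3, so 104. Then 104 / 0.8 = 130. Both figures reproduce, so N = 208 evaluable and 260 recruited.

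**Model for the check.**
- From the protocol: 1:1 allocation, N = 208, SD 20.52, alpha 0.05.
- Assumed: SMART raises adherence by a = 0.5 or 0.6 SD. Baseline and final score correlate at 0.5. A side-effect variable U correlates at −r with adherence and −r with outcome.
- Adherence has **no** effect on outcome.

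**Bias of the adherence coefficient.** Given group and baseline score, adherence and outcome share only U. In SD units the partial coefficient is b = r × r instead of 0. The false indirect effect is a × r² × 20.52 points. For a = 0.6 and r = 0.3 this is 0.6 × 0.09 × 20.52 = 1.1 points. At r = 0.4 and 0.5 it is 2.0 and 3.1 points, against the planned difference of 8.

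**How often the result looks positive.** The result is counted as positive when both paths are significant.
- SE(b) = √[(1 − 0.25 − b²)/208]. At r = 0.3: √(0.7419/208) = 0.0597, z = 0.09/0.0597 = 1.51, and the chance that |z| exceeds 1.97 is 32%.
- SE(a) = 2/√208 = 0.139. For a = 0.5, z = 3.61 and the first path is significant in 95% of trials. For a = 0.6 it is 99%.
- Product at r = 0.3: 0.32 × 0.95 = 31% and 0.32 × 0.99 = 32%.

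Monte Carlo runs of the same model (1,500 to 2,000 trials per scenario) agree within simulation error:

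| r with adherence and outcome | No pathway adjustment, a = 0.5-0.6 | Pathway explains 30% of U (assumed), a = 0.6 |
|---|---|---|
| 0.1 | about 5% | about 5% |
| 0.2 | 10% | 7% |
| 0.3 | 29-32% | 19% |
| 0.4 | 71-77% | about 50% |
| 0.5 | 93-98% | 89% |

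With pathway adjusted, the coefficient becomes b = 0.7r²/(1 − 0.3r²). At r = 0.3 this is 0.063/0.973 = 0.065, smaller than 0.09 but not zero.

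**Sensitivity.**
- N = 260, a = 0.5, no pathway adjustment, r = 0.2 to 0.5: 11%, 36%, 84%, 98%.
- A weaker effect on adherence (a = 0.3, N = 208): 7%, 17%, 44%, 57%.
- If SMART does not change adherence, the rate is at most about 5%.
- A Sobel test instead of joint significance (a = 0.5, N = 208): 5%, 17%, 55%, 88%.
- With U fully measured and adjusted: 4-6% on the joint test, mean indirect effect about 0.

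**Adherence as moderator.** With a constant SMART effect, the group-by-adherence interaction stays near 5% when side effects act equally on adherence in both arms. If they act in SMART only, it is significant in about 12%, 26-28% and 55-58% of trials at r = 0.3, 0.4 and 0.5.

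**The case against.** The strongest reply is that this belongs in the statistical analysis plan. The protocol gives mediation one sentence, its list of confounders is open-ended, and it promises a final plan. Nothing excludes adjustment for side effects. That stands for the detailed covariate list and the form of the interval. It does not remove the point, because the protocol already fixes the product-of-coefficients method and names adherence as a moderator.

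Second, a reader might infer that the planned adjustment does nothing about side effects. The documents do not support that. Treatment pathway is a stratification variable, the models adjust for those variables, and the barrier cited in the background is specifically chemotherapy side effects. Pathway is a partial proxy and lowers the rates, as the table shows. It cannot capture how side effects differ between people on the same pathway.

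Third, the protocol states no null hypothesis and no test for mediation. It speaks of calculating an indirect effect and reporting 95% intervals. The rates above describe how often a conventional criterion would look positive. They are not the error rate of a test that the plan specifies.

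Fourth, no correlation comes from the documents. At 0.2 the excess is mild and the false effect is about half a point (0.6 × 0.04 × 20.52 = 0.5).

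Fifth, the obvious remedy, adjusting for mid-way EORTC scores, has its own bias. Those scores follow about half of the exercise exposure and come from the same instrument as the outcome. In one illustrative simulation with a true indirect effect of 3.1 points, the unadjusted estimate was 4.3 and the mid-way-adjusted estimate 2.1. This objection stands and shapes the fix.

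**Conclusion.** The point holds in a limited form. As written, the mediation analysis can attribute benefit to adherence when there is none, through a common cause that the protocol describes. The excess over 5% depends on three things: SMART raising adherence, which is its aim; side effects correlating with both adherence and outcome at about 0.2 or more; and pathway capturing only part of them. Under the assumed range it runs from slight (7-10% at 0.2) to severe (about 90% or more at 0.5).

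Two stronger readings should be resisted. One is that the moderator analysis will falsely show SMART working better in adherers: this was shown only when side effects drive adherence in the SMART arm alone. Adherence is still unsuitable as a moderator, because allocation changes it. The other is that the trial's main conclusion is at risk: the primary intention-to-treat comparison and the sample size do not depend on this analysis. This is a worthwhile, inexpensive improvement to a secondary question.

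**What to change.** 1. In sections 3 and 9, take adherence off the moderator list and keep factors fixed before randomisation, such as treatment pathway and cancer stage.
2. Keep the mediation analysis. Adjust the adherence-to-outcome model for baseline score, treatment pathway and stage. State the assumption of no unmeasured confounding between adherence and outcome, report a sensitivity analysis over the residual adherence-outcome correlation, and label the indirect effect exploratory.
3. Use the mid-way EORTC symptom scores and the recorded chemotherapy dose reductions or delays only in a secondary sensitivity adjustment. SMART may change them, and conditioning on them can remove real mediation.

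The cost is a few sentences and a little more analysis of data already scheduled. Adherence would no longer be reported as a moderator.

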## 6 Treatment of Participants

### Description and justification for treatments, interventions or methods to be utilised

Those randomised to the experimental group will receive the *SMART* exercise program, as discussed above. Those randomised to the control group will receive usual care. This comprises education regarding the importance of exercise during cancer treatment, a pamphlet/information regarding appropriate off-site exercise groups. Separate oncology physiotherapy provision for patients undergoing chemotherapy treatment involves education strategies and the option to attend a weekly exercise session in the physiotherapy gym. However, exercise intervention as part of routine physiotherapy care for this patient group at RPH is currently through an “opt-in” system and resultant uptake of this service is low. In addition, the control group will receive a phone call from the research team once a month. During this phone call, information regarding healthcare utilisation will be collected and participants will receive generic encouragement to stay active during over the 16-week period.

The trial will run over a three-year period, with recruitment commencing in early 2024. Each participant will provide informed consent, after which they will complete a baseline assessment. On completion of these baseline assessments, participants will be randomised to either the experimental or control group and complete a 16-week intervention phase. Thereafter, all participants will complete a suite of re-assessments, (i) mid-way through the intervention phase, (ii) on completion of the intervention phase and, (iii) 12 months following randomisation.

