## Efficacy assessment

Data collection will require two visits to the Physiotherapy Department at RPH. These assessments will be approximately 90 minutes in duration and will be completed pre-randomisation (baseline assessment) and at the end of the intervention phase. All other data collection will be done by extracting information from medical records, during phone conversations with the participants or by emailing out questionnaires through online formats (e.g. REDCap).

Table 1: Timing of outcomes

|                                                          | Pre-randomisation | Each week during the intervention phase | Mid-way through the intervention phase | On completion of the of intervention phase | 12 months following randomisation |
|----------------------------------------------------------|--------------------------|------------------------------------------------|-----------------------------------------------|---------------------------------------------------|------------------------------------------|
| Descriptive data (age, sex etc)                          | X                        |                                                |                                               |                                                   |                                          |
| EORTC QLQ C30 with BR45 (health-related quality of life) | X                        |                                                | X                                             | X                                                 | X                                        |
| EQ-5D-5L                                                 | X                        |                                                | X                                             | X                                                 | X                                        |
| Grip strength                                            | X                        |                                                |                                               | X                                                 |                                          |
| Deltoid, bicep and quads strength                        | X                        |                                                |                                               | X                                                 |                                          |

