| SRBAI                                                    | x                        |                                                | x                                             | x                                                 | x                                        |
| PANAS                                                    | x                        |                                                | x                                             | x                                                 | x                                        |
| Participation in exercise                                |                          | X                                              |                                               |                                                   |                                          |
| Healthcare utilisation                                   |                          | X                                              |                                               |                                                   |                                          |
| iMTA (absenteeism / presenteeism)                        |                          |                                                | X                                             | X                                                 | X                                        |
| Acceptability/ feasibility                               |                          |                                                |                                               | x                                                 |                                          |
| Exit interview                                           |                          |                                                |                                               | x                                                 |                                          |

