- What is the health care utilisation, absenteeism and presenteeism over the 12 months following randomisation?

This is an exploratory question and data will be described using mean and standard deviation.

*The third secondary research question is:*

- Does performance on tests of peripheral muscle force-generating capacity and exercise tolerance, change with test repetition (i.e. is there a learning effect)?

This will be assessed using one-way repeated measures analysis of variance (ANOVA). That is, for each participant, data collected over consecutive trials (5 attempts for each measure of muscle force and 2 attempts for the 6MWT) compared to explore if there is an effect of test repetition on these outcomes.

*The fourth secondary research question is:*

What is the minimal detectable difference in health-related quality of life and exercise tolerance?

This will be assessed using anchor-based approach via a Receiver Operating Characteristic curve. This curve will determine the optimal operating point to discriminate between participants who rate themselves as changed vs unchanged at the end of the SMART program.

*The fifth secondary research question is:*

Do psychological determinants of behavioural change, such as capability, opportunity, and motivation affect adherence to the SMART program and physical activity maintenance?

This will be assessed using correlations and a Multiple Regression Analysis of the data from psychological determinant measures (COM-B factors, impairment in functioning, intention, self-efficacy, habit, and mood) across all time-points for each participant. Data from the exit interviews will also be analysed using qualitative methods (such as thematic analysis) to explore participants' reasons for engagement (or lack of engagement).

*The sixth secondary research question is:*

Does the SMART program improve mood, and does mood influence adherence to the program and physical activity maintenance?

This will be assessed using correlations between mood data from the PANAS (across all timepoints) and physical activity engagement.

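### Healthcare utilisation and exercise participation are scheduled only during the 16-week intervention phase, so the 12-month utilisation question and the activity-maintenance clauses of two other questions have no scheduled data after week 16

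*Protocol*

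**What the plan says.** Section 3 (Trial Aims / Objectives / Hypotheses) sets the second secondary question as "What is the health care utilisation, absenteeism and presenteeism over the 12 months following randomisation? (descriptive analyses only", and section 9 (Statistics and Interim Analysis) repeats it as "What is the health care utilisation, absenteeism and presenteeism over the 12 months following randomisation" and calls it exploratory. The fifth secondary question asks whether psychological determinants "affect adherence to the SMART program and physical activity maintenance". The sixth asks whether the program improves mood, and "does mood influence adherence to the program and physical activity maintenance". The Trial Summary uses maintenance to mean activity kept up once the program is over.

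The timing-of-outcomes table under Efficacy assessment in section 7 has a row for "Participation in exercise" and a row for "Healthcare utilisation". Each carries a single mark, in the column headed "Each week during the intervention phase". The cells for 12 months after randomisation are empty in both rows.

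The text agrees with the table. Under Other Variables in section 7, both variables come from the weekly supervised sessions in the experimental group, from monthly phone calls in the control group, and from exercise diaries in both. The supervised sessions are part of the 16-week program. Section 6 describes the calls together with that same period: besides being asked about healthcare use, "participants will receive generic encouragement to stay active during over the 16-week period".

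**The concern.** Three secondary questions need information from after week 16 on healthcare use or on exercise actually done, and the schedule does not provide for either. For questions five and six the mismatch is marked: the psychological measures and mood are collected again at 12 months, but the activity they are meant to explain is not.

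Two things are at stake. First, the utilisation question exists to guide patients' expectations over a year, and the scheduled data describe only the first 16 weeks, when treatment and trial contact may differ from the rest of the year. Second, maintenance is part of the trial's rationale: the Background cites a review in which activity levels were maintained in only four of ten trials, and section 15 lists effects on maintenance among the findings likely to matter most. Once participants have passed their 12-month assessment, the missing information cannot be reliably rebuilt, and an analysis plan cannot supply data that were never collected.

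**Working it through.** The check compares objectives with the schedule. The only calculated design figure in the protocol is the sample size for the primary outcome (104 per group, 130 after 20% drop-out). It reproduces, since 104 / 0.8 = 130 and power with 104 per group is 80.3%. The present point does not depend on it.

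**Inputs**
- Length of the intervention phase: 16 weeks (section 4, Trial Duration/Schedule).
- Horizon of the utilisation question: 12 months, taken as 52 weeks (sections 3 and 9).
- Collection windows: the timing table in section 7.

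**Each question against what is scheduled**

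| Secondary question | Component | Scheduled collection | Covered? |
|---|---|---|---|
| 2 | Absenteeism and presenteeism | iMTA mid-way, at end of intervention and at 12 months | Yes |
| 2 | Healthcare utilisation over 12 months | Intervention phase only | In part |
| 5 | Psychological determinants | COM, WSAS, intention, BTSES, HTQ and SRBAI at four time points including 12 months | Yes, as predictors |
| 5, 6 | Adherence to the program | Exercise participation during the intervention phase | Yes |
| 6 | Effect on mood | PANAS at four time points including 12 months | Yes |
| 5, 6 | Activity maintenance after the program | None | No |

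**Coverage of the utilisation window**
- Scheduled: 16 / 52 = 0.308, or 31%.
- Not scheduled: 52 − 16 = 36 weeks; 36 / 52 = 0.692, or 69%.

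**Coverage of the maintenance period**
- Weeks 17 to 52 are 36 weeks, and exercise participation is scheduled in 0 of them.

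**Could another 12-month instrument stand in?** The table's 12-month column contains the EORTC questionnaires, EQ-5D-5L, COM, WSAS, intention, BTSES, HTQ, SRBAI, PANAS and iMTA. None is described in section 7 as recording healthcare visits or exercise performed. Intention and habit automaticity are treated as determinants of the behaviour, so using them as the maintenance outcome would put the same construct on both sides of the analysis.

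**Is the pattern an artefact of a broken table?** Probably not. The adjacent iMTA row shows its 12-month mark in the expected place, and the narrative under Other Variables gives the same collection routes as the table.

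**The case against.** The strongest reply is that the protocol leaves several routes open. The wording in section 6 ties the encouragement to 16 weeks but does not expressly end the monthly calls. The exercise diaries have no stated end date. Data management (section 9) mentions stored heart-rate and activity metrics from wearables, with no stated wear period. Efficacy assessment allows other data to come from medical records, phone conversations or e-mailed questionnaires. The questionnaires are in appendices that are not shown.

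This bears on the wording. A reader might infer that there will be no data at all after week 16. The document does not go that far; it shows only that none are scheduled. The mismatch itself remains, because none of these routes is assigned to utilisation or exercise after week 16, and Other Variables defines utilisation by participant recall.

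A second reply is that the consequence is limited, and this stands. Question two is descriptive and exploratory, and the maintenance clauses are secondary and correlational. The randomised comparison of quality of life at 16 weeks, its 12-month follow-up and the sample size are untouched. A reader might infer that questions two, five and six fail as a whole, but most of their components are covered. Nor does the protocol say that 16-week figures would be reported as 12-month figures; the risk is that the question as worded invites it.

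A reader might also object to describing utilisation by mean and standard deviation. That is a reporting choice unrelated to the schedule, and it forms no part of this point.

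Finally, a single 12-month questionnaire would ask for recall over about 36 weeks, against weekly or monthly recall during the intervention phase. This is a fair criticism of the simplest remedy, and the fix must acknowledge it.

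**Conclusion.** The inconsistency is real but confined to two places. The utilisation component of question two has scheduled collection for 16 of 52 weeks (31%), and the maintenance clauses of questions five and six have no scheduled outcome measure. The conclusion rests on three readings: that 12 months means 52 weeks from randomisation; that the monthly calls and diaries stop with the 16-week phase, which the table and section 6 indicate but do not state outright; and that maintenance means activity after the program, as in the Trial Summary.

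The percentages describe the schedule and are not a forecast of lost data. The protocol does not support the stronger reading that three research questions are unanswerable or that the trial's main results are at risk. This should be fixed, because the information is hard to recover later and the change is small, but the validity of the primary analysis does not depend on it.

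**What to change.** Preferred change:
- Add the exercise items already described under Other Variables (current minutes of moderate or vigorous activity, and resistance training) and the utilisation items to the 12-month questionnaire set, with the same wording and method in both groups.
- Mark the corresponding 12-month cells in the timing table.
- Supplement utilisation for weeks 17 to 52 with emergency visits and admission days from the Royal Perth Hospital records.
- State the limits: recall over about 36 weeks is less reliable than the weekly or monthly recall used earlier, and the hospital's records miss care given elsewhere, which matters in a trial that includes rural and remote participants. A short e-mailed questionnaire between week 16 and month 12 would shorten the recall window.
- State whether the monthly calls, diaries and wearable monitoring end at week 16.

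The cost is a minor amendment, a few extra items in a questionnaire set already planned for 12 months, some record extraction, and modest participant burden (a little more if the interim questionnaire is used).

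If the sponsor does not want the extra collection, restrict the utilisation part of question two to the 16-week period, leaving absenteeism and presenteeism at 12 months, and remove maintenance from questions five and six in sections 3 and 9, with the matching entry in section 15. That costs only a wording change, but gives up the maintenance question that the Background uses to motivate the trial.
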